**PSMA guided approach for bIoCHEmical relapse after prostatectomy-A prospective observational study-PSICHE**

**1. INTRODUCTION**

**1.1. Background and overall rationale for the study.**

Up to date, salvage prostate bed radiotherapy (SRT) represents the cornerstone therapeutic approach in the setting of early biochemical relapse (BR) after radical prostatectomy (RP) (defined as a detectable or rising PSA value after surgery >0.2 ng/ml) [Thompson 2013///Pisansky 2019///Tendulkar 2016]. However, recent evidence from literature induced European Association of Urology to allow use of 68Ga-PSMA-11 PET/CT to restage all prostate cancer (pCa) patients affected by BR after radical therapy [Cornford 2017], based on its higher accuracy if compared with other metabolic (i.e choline or fluciclofine) imaging [Afshar-Oromieh 2017///Calais 2019]. This prompted significant changes in current management of patients in this setting, leading to the development of imaging-guided approaches [Ost 2015], aimed to postpone palliative androgen deprivation therapy (ADT) [Ost 2018]. Similar approaches already showed to affect clinical management after restaging, but prospective assessment of PSMA-guided therapy to control the disease in the recurrent setting is lacking [Deandreis 2020]. In this setting, different approaches are already available in routine clinical practice (e.g prostate bed radiotherapy, Stereotactic radiotherapy on positive nodal disease or metastatic lesions, androgen deprivation therapy). Prospective evaluation of a standardized approach for these patients could provide interesting insights about the impact of 68Ga-PSMA-11 PET/CT on following clinical outcomes. With this purpose, we designed a prospective, observational study aimed to explore the prognostic factors related to progression free survival after 68Ga-PSMA-11 PET/CT restaging and subsequent treatment. To explore the correlation between PSMA PET/CT findings and predictive biomarkers, aiming to detect a subgroup of patients in whom PSMA PET/CT may have different detection rate, we included a secondary endpoint to evaluate the expression of a specific micro-RNA (miRNA) panel correlated to PSMA gene expression [Erdmann 2014].

**2. OVERVIEW OF STUDY DESIGN**

**2.1. Hypothesis:**

This observational study was designed to evaluate PFS after PSMA-PET/CT based salvage approach for patients affected by BR after RP.

- 1. **Study design**

This is a prospective observational multicenter study including patients treated with upfront RP +/- postoperative prostate bed radiotherapy, with histological result of Prostate adenocarcinoma, affected by BR (defined as PSA > 0.2 ng/ml) with a PSA at recurrence < 1 ng/ml. Patients will be staged with centralized 68Ga-PSMA PET/CT and treated with a pre-defined approach based on 68Ga-PSMA PET/CT findings, according to routine clinical practice:

| Negative 68Ga-PSMA PET/CT or positive findings within prostate bed | Prostate bed RT*, **, *** |
| --- | --- |
| 68Ga-PSMA PET/CT detecting pelvic nodal recurrence (defined as nodal disease < 2 cm under aortic bifurcation) amenable with stereotactic body radiation therapy (SBRT) on all sites of disease | SBRT to positive nodal disease |
| Abdominal nodal or bone oligometastatic disease (defined as < 3 non visceral lesions, according to Association of Radiotherapy and Clinical Oncology (AIRO) definition [D’angelillo 2019]) amenable with stereotactic body radiation therapy (SBRT) on all sites of disease | SBRT on all sites of disease |
| Abdominal nodal or bone metastatic disease (> 3 lesions or non-amenable with SBRT) and/or visceral disease. | ADT+/-other systemic therapies available for metastatic hormone sensitive pCa at physician discretion |

**For patients who did not previously received prostate bed RT, dose intensification (e.g 72-74 Gy in 36-37 fractions or equivalent dose/fractionation schedules) will be provided* *in case of positive PSMA/PET-CT findings inside prostate bed. In this case, Stereotactic Salvage RT (e.g. 35 Gy in 5 fractions on macroscopic recurrence) is allowed within site-specific study protocols.*

*** For patients who already received prostate bed RT in postoperative setting with negative findings within prostate bed, observation and PSMA-PET/CT re-staging at further PSA progression (defined as > 25% PSA increase if compared to PSA at recurrence) will be performed*

**** For patients who already received prostate bed RT in postoperative setting with positive findings within prostate bed, both observation and PSMA-PET/CT re-staging at further PSA progression or prostate bed retreatment (e.g SBRT for a total dose of 30 Gy in 5 fractions) will be allowed according to clinician choice*

Planned size of the overall study population is 180 patients. Data about demographics, PSA, comorbidities and current drug therapies up to 45 days prior to enrollment will be collected at baseline. The study will consist in the observation of outcomes after 68Ga-PSMA PET/CT staging and following postoperative tailored management. Total planned duration of the study is 84 months, consisting in 36 months enrollment period and a later phase of 48 months in which patients will continue to be submitted to periodic checks every 3 months.

**2.3. Study design rationale**

Standard approach for BR after RP is SRT [Thompson 2013]. However, emerging imaging modalities, such as 68Ga-PSMA PET/CT, allowed to effectively estimate location and actual burden of disease, and are currently used in clinical practice. A tailored approach based on 68Ga-PSMA PET/CT findings allows to increase clinical outcomes and reduce unnecessary toxicity (e.g prostate bed RT in patients with sublinical metastatic disease, undetectable with conventional staging). However, prospective data about this issue could help to accurately assess prognostic factors associated to clinical outcomes after a tailored postoperative approach.

**3. STUDY OBJECTIVES**

**3.1. Primary objectives**

Primary objective of the study will be to explore prognostic factors correlated with clinical outcomes in the enrolled cohort.

**3.2. Secondary objectives**

-To explore prognostic factors correlated with Overall survival, defined as time between surgery and death

-To record 2 years Health related quality of life

-To record the proportion of management changes induced by positive PSMA PET/CT results

-To assess the association between PSMA PET/CT detection rate and baseline detection of a specific panel of miRNA (miR-186, miR-26a, miR-374a, miR-410, miR-660)

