**3.3 Study endpoints**

*Primary endpoint*

Primary objective of the study will be to explore prognostic factors correlated with rate of 2 years PFS. PFS is defined as time from end of salvage treatment performed at first relapse to documented biochemical progression or radiological progression (or both), death from any cause or censoring at date of last follow-up. Biochemical progression is defined as the date in which a PSA increase above 0.2 ng/ml for patients with a PSA nadir < 0.2 ng/ml or 2 consecutive PSA increases >25% if compared to nadir in patients with a PSA nadir > 0.2 ng/ml is detected. Radiological progression will be defined as the occurrence of any new lesion detectable with PSMA PET/CT and/or any other molecular/radiological exam, which will be performed in case of biochemical or clinical progression

*Secondary endpoints*

- Explore prognostic factors correlated with Overall survival (defined as time between end of tailored treatment after 68Ga-PSMA PET/CT and death)

- Explore prognostic factors correlated with Cause specific survival, defined as time between end of tailored treatment and death for prostate Cancer

- Explore prognostic factors correlated with Radiological PFS, defined as the occurrence of any new lesion detectable with PSMA

PET/CT and/or any other molecular/radiological exam, which will be performed in case of biochemical or clinical progression

-Record rate of patients with impaired quality of life measured by EORTC QLQ-C30 and EORTC QLQ-PR25 at 2 years (defined as decrease by 10 points in global health scale and functional scales or increase by 10 points in symptoms scales compared with baseline, without later improvement superior by 10 points)

-To assess the proportion of management changes induced by positive PSMA PET/CT results

-To assess the association between PSMA PET/CT detection rate and baseline detection of a specific panel of miRNA (miR-186, miR-26a, miR-374a, miR-410, miR-660)

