**4. STUDY POPULATION**

**4.1. Inclusion Criteria**

Each potential subject must satisfy all of the following criteria to be enrolled in the study.

- Signed informed consent
- Age >18
- Patient suitable for 68Ga-PSMA PET/CT re-staging according to clinical practice (Previous radical prostatectomy with histological result of Prostate adenocarcinoma +/-postoperative prostate bed radiotherapy (adjuvant or salvage setting), with a biochemical relapse defined as a PSA > 0.2 and <1

1. **Exclusion Criteria**

- ADT administration within 6 months from studyenrollment
- Persistent elevation of PSA after RP measured within 16 weeks from surgery (> 0.1 ng/ml)

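### Sections 3.2 and 3.3 start overall survival at different dates; the surgery date adds immortal time unless delayed entry is used, and end of treatment is not defined for every patient

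*Protocol*

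**What the plan says.** Section 3.2 (Secondary objectives) lists: "To explore prognostic factors correlated with Overall survival, defined as time between surgery and death". Prostatectomy is the only surgery in the protocol, so that is the date meant.

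Section 3.3 (Study endpoints) gives the same endpoint as "Overall survival (defined as time between end of tailored treatment after 68Ga-PSMA PET/CT and death". Two neighbouring endpoints there use a similar clock: "Cause specific survival, defined as time between end of tailored treatment and death for prostate Cancer" and, for the primary endpoint, "PFS is defined as time from end of salvage treatment performed at first relapse to documented biochemical progression".

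Section 4 fixes who can enter. A patient must have had a prostatectomy and then present "with a biochemical relapse defined as a PSA > 0.2 and <1", and must give consent ("Signed informed consent"). The exclusion criteria remove those with "Persistent elevation of PSA after RP measured within 16 weeks from surgery (> 0.1 ng/ml").

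The treatment table and footnotes under Study design in Section 2 allow observation for some previously irradiated patients, and assign ADT with or without other systemic therapy, with no stated duration, to patients with more extensive disease. The same section sets the study length, "consisting in 36 months enrollment period and a later phase of 48 months".

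**The concern.** One endpoint with two start dates gives two survival curves and possibly two sets of prognostic factors. Nothing in the protocol says which definition governs. If this is left open until the data are in, the choice could be made with the results in view. OS and cause-specific survival could also end up on different clocks in the same report.

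The two dates are not equally harmless. Patients are selected after surgery, at relapse. Anyone who died between prostatectomy and enrolment cannot be in the cohort, so a clock started at surgery contains a stretch in which no death can be observed. The stated objective is to find prognostic factors. A factor that goes with a longer interval from surgery to relapse would be credited with that stretch and look protective, and a factor that goes with a shorter interval would look harmful.

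**Working it through.** The protocol gives no OS rate, event count or OS sample size, so there is no OS figure to reproduce. The contradiction is shown by the text. The calculations only size what follows if the surgery clock is used as written.

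**1. The start dates side by side**

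| Endpoint | Section | Clock starts |
|---|---|---|
| OS | 3.2 | surgery |
| OS | 3.3 | end of tailored treatment |
| Cause-specific survival | 3.3 | end of tailored treatment |
| PFS | 3.3 | end of salvage treatment |

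The surgery origin is the odd one out.

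**2. Why the surgery interval is immortal.** Entry needs prostatectomy, then relapse, then consent. PSA persistence within 16 weeks of surgery excludes a patient, so relapse cannot simply be persistence after the operation. Every enrolled patient was therefore alive throughout the interval from surgery to enrolment. The protocol mentions no delayed entry.

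**3. Share of person-time that is immortal (illustrative).** Follow-up runs from 48 months (last patient in) to 36 + 48 = 84 months (first patient in), that is 4 to 7 years. With uniform accrual and no deaths or drop-out, the mean is (4 + 7)/2 = 5.5 years. For an assumed surgery-to-enrolment interval of L years, the immortal share is L/(L + 5.5):

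- L = 1: 1/6.5 = 15%
- L = 3: 3/8.5 = 35%
- L = 8: 8/13.5 = 59%

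With D deaths, a crude rate D/(L + 5.5) is lower than D/5.5 by exactly that share.

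**4. Effect on a 5-year survival figure (illustrative).** Assume a constant hazard h per year after entry and a fixed interval L. From the later origin, S(5) = exp(−5h). On the naive surgery clock, S(5) = exp(−h(5 − L)), because the first L years are flat.

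| h | Later origin | L = 1 | L = 2 | L = 3 | L = 5 |
|---|---|---|---|---|---|
| 0.02 | 90.5% | 92.3% | 94.2% | 96.1% | 100% |
| 0.03 | 86.1% | 88.7% | 91.4% | 94.2% | 100% |
| 0.05 | 77.9% | 81.9% | 86.1% | 90.5% | 100% |

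The gap runs from about 2 points (92.3 − 90.5) to about 22 points (100 − 77.9).

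**5. Effect on a prognostic factor (illustrative).** One simulated data set per scenario: 6,000 patients, follow-up uniform on 4 to 7 years, hazard 0.03 per year, and a binary factor with no true effect. Cox hazard ratios:

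| Mean interval, factor absent vs present | From treatment | Naive from surgery | From surgery, delayed entry |
|---|---|---|---|
| 3 vs 3 years | 1.06 | 1.05 | 1.06 |
| 4 vs 2 years | 1.06 | 1.49 | 1.10 |
| 5 vs 1.5 years | 1.06 | 1.91 | 1.12 |

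The 1.06 for a null factor is chance in a single data set, so the shift is what matters: 1.49/1.06 = 1.41 and 1.91/1.06 = 1.80. There is essentially no shift when the factor is unrelated to the interval, and delayed entry removes most of it otherwise.

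**6. The Section 3.3 origin.** A patient under observation has no treatment to end. A patient on systemic therapy has no end defined in the protocol. For both, the start of the OS clock is unspecified. For treated patients, the clock starts after a short stretch on study that they have already survived.

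**The case against.** The best reply is that the endpoints section is the operative one. Section 3.3 puts OS, cause-specific survival and PFS at or near the same start, so Section 3.2 is a stray line and no biased analysis may ever be run. A statistical analysis plan, not shown here, could also specify delayed entry. This stands in part: bias is a consequence of one reading, not an established feature of the analysis. It does not remove the contradiction, since such a plan would still inherit two definitions from the protocol.

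Some stronger readings are tempting but not supported:

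- A reader might infer that the prognostic analysis as a whole is biased. Only factors associated with the surgery-to-enrolment interval are affected. That is plausible for the recorded stage, margin status and Gleason score, but the protocol does not establish it.
- A reader might take 15%, 35% and 59% as estimates for this trial. They rest on assumed intervals and a simplified follow-up (Section 6.3 itself plans for 5% drop-out), and they describe a crude death rate that the protocol does not say it will report.
- A reader might say that treatment never ends for patients on ADT. The protocol gives no duration, so all that can be said is that no end is defined.
- A reader might assume the needed dates are already recorded. Section 6.1 lists earlier treatments and the staging PET/CT but names no date for either.

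It is also fair that OS is secondary and exploratory, and that the sample size rests on 2-year PFS, which neither OS definition touches.

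**Conclusion.** The point holds in this form. The contradiction between Sections 3.2 and 3.3 is exact and depends on no assumption. Bias is conditional on the surgery clock being used without delayed entry. In that case survival is overstated, by about 2 to 22 percentage points at 5 years for assumed intervals of 1 to 5 years and hazards of 0.02 to 0.05 per year, and hazard ratios are distorted for factors tied to the interval. The protocol supplies neither the interval nor the hazard, so these sizes are illustrations.

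Adopting the Section 3.3 wording unchanged would settle the contradiction but leave some patients without a start date. The point should be corrected before analysis. It does not threaten the primary endpoint's sample size.

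**What to change.** Delete the surgery-based definition in Section 3.2. In Sections 3.2 and 3.3, use one origin that every patient has for both OS and cause-specific survival. The index PSMA PET/CT date or the enrolment date would serve; the choice between them is a preference.

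Deal with PFS in the same edit. Section 3.3 now starts it at the end of salvage treatment, so moving only the survival endpoints would split origins that are at present aligned. Either move PFS to the common date or state why it differs and how patients without an end-of-treatment date are handled.

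If time since surgery is of interest, analyse it only with delayed entry at the common date. Adding the surgery-to-relapse interval as a covariate may repair hazard ratios, but it leaves the flat first stretch in the survival curve, so it is not a substitute.

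The cost is wording in two sections and a check that the chosen date is recorded (and the surgery date, if delayed entry is wanted). Reported survival times become shorter than under Section 3.2 and slightly longer than under Section 3.3. No treatment rule changes.

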**3.3 Study endpoints**

*Primary endpoint*

Primary objective of the study will be to explore prognostic factors correlated with rate of 2 years PFS. PFS is defined as time from end of salvage treatment performed at first relapse to documented biochemical progression or radiological progression (or both), death from any cause or censoring at date of last follow-up. Biochemical progression is defined as the date in which a PSA increase above 0.2 ng/ml for patients with a PSA nadir < 0.2 ng/ml or 2 consecutive PSA increases >25% if compared to nadir in patients with a PSA nadir > 0.2 ng/ml is detected. Radiological progression will be defined as the occurrence of any new lesion detectable with PSMA PET/CT and/or any other molecular/radiological exam, which will be performed in case of biochemical or clinical progression

*Secondary endpoints*

- Explore prognostic factors correlated with Overall survival (defined as time between end of tailored treatment after 68Ga-PSMA PET/CT and death)

- Explore prognostic factors correlated with Cause specific survival, defined as time between end of tailored treatment and death for prostate Cancer

- Explore prognostic factors correlated with Radiological PFS, defined as the occurrence of any new lesion detectable with PSMA

PET/CT and/or any other molecular/radiological exam, which will be performed in case of biochemical or clinical progression

-Record rate of patients with impaired quality of life measured by EORTC QLQ-C30 and EORTC QLQ-PR25 at 2 years (defined as decrease by 10 points in global health scale and functional scales or increase by 10 points in symptoms scales compared with baseline, without later improvement superior by 10 points)

-To assess the proportion of management changes induced by positive PSMA PET/CT results

-To assess the association between PSMA PET/CT detection rate and baseline detection of a specific panel of miRNA (miR-186, miR-26a, miR-374a, miR-410, miR-660)

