**6. STUDY EVALUATIONS**

**6.1 Pre­Treatment Evaluation**

Baseline evaluations include:

- - demographics data;
  - active co­morbidities and current medical treatments;
  - Pathological staging, margin status, PSA value and Gleason Score at the time of prostate cancer diagnosis;
  - previous treatments for prostate cancer;
  - Baseline PSA at BR
  - Imaging procedures:
- Staging with PSMA PET/CT
  - assessment of Performance Status with the Eastern Cooperative Oncology Group (ECOG) Score;
  - Baseline Quality of life assessment measured by EORTC QLQ-C30 and EORTC QLQ-PR25 (baseline evaluation should be performed before radiotherapy beginning);
  - Blood samples to detect baseline expression of a specific panel of miRNA (miR-186, miR-26a, miR-374a, miR-410, miR-660)
  1. **Evaluation During Treatment**

Patients will be evaluated as follows:

- After initial PSMA PET/CT, treatment modalitywill be recorded to assess the proportion of management changes induced by positive PSMA PET/CT results
- every 3 months from therapy start with ECOG Score EORTC QLQ-C30 and EORTC QLQ-PR25
- PSA value every 3 months from therapy start
- PSMA PET/CT will be repeated in case of biochemical progression, defined as a PSA increase above 0.2 ng/ml for patients with a PSA nadir < 0.2 ng/ml or 2 consecutive PSA increases >25% if compared to nadir in patients with a PSA nadir > 0.2 ng/ml is detected.

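### The primary PFS clock starts at the end of salvage treatment for first relapse, an origin that does not fit every management group the protocol enrols

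*Protocol*

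**What the plan says.** Section 3.3 of the protocol fixes the origin of the primary endpoint: "PFS is defined as time from end of salvage treatment performed at first relapse to documented biochemical progression or radiological progression (or both". The definition also counts death from any cause as an event and censors at last follow-up.

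Other sections decide which patients this must cover:

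- **Eligibility (section 4.1).** Earlier bed radiotherapy is allowed: "postoperative prostate bed radiotherapy (adjuvant or salvage setting), with a biochemical relapse defined as a PSA > 0.2 and <1".
- **Management of previously irradiated patients (section 2, footnotes to the management table).** With negative findings in the prostate bed, "observation and PSMA-PET/CT re-staging at further PSA progression (defined as > 25% PSA increase if compared to PSA at recurrence) will be performed". With positive findings there, the clinician may choose observation or retreatment.
- **Management of extensive, visceral or non-SBRT-amenable disease (section 2, last row of the table).** "ADT+/-other systemic therapies available for metastatic hormone sensitive pCa at physician discretion". No duration is stated.
- **Follow-up (section 6, evaluation during treatment).** "PSA value every 3 months from therapy start".

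Overall survival has other origins. Section 3.3 has it "defined as time between end of tailored treatment after 68Ga-PSMA PET/CT and death", while section 3.2 says "To explore prognostic factors correlated with Overall survival, defined as time between surgery and death".

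**The concern.** A PFS definition needs a time zero that every analysed patient has, and that comes before the events to be counted. Here the origin depends on the treatment given. Treatment is assigned by PET result and prior radiotherapy, and both are obvious candidates for the prognostic analysis that is the primary objective.

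Where the rule yields no date, someone must improvise: leave the patient out, use another date, or wait for a later salvage treatment. Leaving patients out removes them selectively. Waiting for a later treatment places the PSA progression that prompted re-staging before time zero, where it is not counted. Either way, the comparison by PET result or prior radiotherapy partly reflects how the clock was set. A larger sample does not cure that.

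**Working it through.** **Step 1. Apply the stated origin to each management group.**

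| Group | Does the stated origin give a date? |
| --- | --- |
| No prior radiotherapy; bed RT or SBRT for the study relapse | Yes |
| Prior adjuvant RT; SBRT or bed retreatment for the study relapse | Yes, if the study relapse is the first |
| Prior RT, observed (bed negative, or bed positive at clinician's choice) | No treatment for the study relapse, so no end date |
| ADT with or without other systemic therapy | Undefined: no duration or end stated, and progression on therapy could precede it |
| Prior RT given in the salvage setting | Read literally, the end of that earlier RT, before enrolment |

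Observed patients also have no therapy start from which to count the 3-monthly PSA visits.

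**Step 2. Test the last row against the event rule.** Section 3.3 counts a PSA above 0.2 ng/ml as biochemical progression when the nadir was below 0.2. If PSA fell below 0.2 after the earlier salvage radiotherapy, the PSA above 0.2 that qualifies the patient under section 4.1 already meets that rule. On the literal wording, such a patient enters with the event behind them.

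The rest of the protocol points elsewhere. Section 1.1 states the aim as PFS after PET restaging and the treatment that follows. Section 2.1 speaks of PFS after a PET-based salvage approach. The overall survival origin in section 3.3 names the tailored treatment after PET. These are in conflict with the words *first relapse*.

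**Step 3. Reproduce the planned precision (section 6.3).** Inputs: p = 0.80, margin d = 0.06, 95% confidence (z = 1.96).

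- n = z²p(1 − p)/d² = 3.8416 × 0.16/0.0036 = 170.7, so 171. The protocol states 172, which agrees within rounding.
- 171/0.95 = 180, the stated target.
- Exact binomial intervals at 80% are 72.7–86.1% (N = 150), 71.7–86.8% (N = 120) and 70.3–87.7% (N = 90). They match the stated 73–86, 72–87 and 70–88.

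The sample size arithmetic is not at fault.

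**Step 4. Precision if patients without a usable origin are dropped.** Half-width = 1.96 × √(0.16/m), with m = 172 × (1 − f). The share f is not in the protocol and is assumed.

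| f (assumed) | m | Half-width, points |
| --- | --- | --- |
| 0 | 172 | 6.0 |
| 10% | 155 | 6.3 |
| 20% | 138 | 6.7 |
| 30% | 120 | 7.2 |
| 40% | 103 | 7.7 |

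**The case against.** The strongest defence is that the intended origin is clear: the end of the PET-guided treatment. Sections 1.1 and 2.1 and the overall survival wording support this, and an end-of-treatment origin is a legitimate choice in an observational study of outcome after treatment. That largely answers the prior-salvage problem, which is a conflict of wording and not a settled plan to start the clock before enrolment. It does not help observed patients, who have no such treatment. It does not supply an end date for systemic therapy either.

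Three stronger readings are tempting, and the protocol does not support them.

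- **That 2-year PFS cannot be computed for the cohort.** Patients given bed radiotherapy or SBRT for the study relapse have a usable end date, apart from the *first relapse* wording.
- **That the end of ADT never arrives.** The protocol gives no duration, but it does not say treatment is indefinite. Undefined is as far as the text goes.
- **That the pooled rate shifts by 8 points per 10% of the cohort,** from 0.10 × (0 − 0.80). This needs the literal reading for prior-salvage patients, and every one of them relapsing within 2 years of the earlier radiotherapy. The protocol's stated aim contradicts the first condition, and it gives no data on the second.

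It also stands that the precision loss is tolerable. Section 6.3 accepts N = 90, and even the assumed 40% leaves 103. Events between PET and the end of a radiotherapy course, and visits counted from therapy start, are matters of weeks and carry little weight in a 2-year rate.

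A statistical analysis plan could add a fallback date. The origin is fixed explicitly in the protocol, though, and no section of it offers a substitute.

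**Conclusion.** The point holds in limited form. The stated origin is missing for observed patients, undefined for systemically treated patients, and ambiguously worded for those with prior salvage radiotherapy. What suffers is the whole-cohort 2-year PFS and the comparisons by PET result and prior radiotherapy, not the estimate among patients irradiated for the study relapse.

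If the affected patients are simply dropped, the half-width goes from 6.0 to between 6.3 and 7.7 points for assumed shares of 10% to 40%. The protocol gives no group sizes, so that range is illustrative, and no size can be put on the bias. The case for change rests on selection or misdating that follows the candidate prognostic factors. For observed patients this comes directly from the text. For systemic therapy it rests on the absence of any stated end.

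**What to change.** Amend section 3.3 so that PFS runs, for every patient and whatever management follows, from the date of the index (enrolment) 68Ga-PSMA PET/CT. Replace the reference to first relapse with wording tied to the relapse that qualified the patient for the study. Count the PSA nadir and progression only from the index date, so that the qualifying PSA cannot itself be an event.

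Keep PFS from the end of radiotherapy as a sensitivity analysis among patients irradiated for the index relapse. This preserves comparability with the 80% planning figure, which section 6.3 describes as PFS after salvage radiotherapy alone.

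In the same amendment, reconcile the overall survival origins in sections 3.2 and 3.3, and state the date from which visits are counted for patients who start no therapy. The re-staging trigger for observed patients in section 2 (a rise of more than 25% over PSA at recurrence) and the progression rule in section 3.3 (two consecutive increases when the nadir is above 0.2) also differ. A new origin does not settle that, so those passages must be reconciled separately.

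The cost is small. All patients are staged with the index PET, so no new data item is needed and no treatment changes. All 172 evaluable patients then contribute, and the half-width stays at 6.0 points at 80%. The downside is that PFS times will include the weeks from PET to the end of treatment, so the quantity differs slightly from the planning figure and the 2-year rate may look a little less favourable.

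### PFS ignores anticancer treatment started before the progression rule is met, and Section 6 does not list it for recording, so 2-year PFS can be overstated as a measure of the PSMA-guided salvage treatment

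*Protocol*

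**What the plan says.** Protocol Section 3.3 sets the clock and the events. The start: "PFS is defined as time from end of salvage treatment performed at first relapse". The end: "documented biochemical progression or radiological progression (or both), death from any cause or censoring at date of last follow-up". Biochemical progression depends on the nadir. When the nadir lies under 0.2 ng/ml, one value over that threshold is enough. When it lies over the threshold, Section 3.3 requires "2 consecutive PSA increases >25% if compared to nadir in patients with a PSA nadir > 0.2 ng/ml". Radiological progression is a new lesion on imaging, "which will be performed in case of biochemical or clinical progression". Starting a later anticancer treatment is not named as an event, as a reason for censoring, or as something to be handled separately.

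Section 6 (Evaluation During Treatment) asks for the treatment chosen after the first PET/CT. After that it lists performance status, questionnaires, "PSA value every 3 months from therapy start" and a repeat PET/CT at biochemical progression. It does not list start dates of later ADT, systemic therapy or local treatment. The exclusion criteria restrict ADT only around enrolment.

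The Study design footnotes in Section 2 cover patients who have already had prostate bed radiotherapy. If the bed is negative, "observation and PSMA-PET/CT re-staging at further PSA progression (defined as > 25% PSA increase if compared to PSA at recurrence) will be performed". If the bed is positive, the clinician may choose observation with re-staging "or prostate bed retreatment (e.g SBRT for a total dose of 30 Gy in 5 fractions) will be allowed according to clinician choice".

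**The concern.** The clock starts at the end of the salvage treatment, so PFS is meant to describe how long that treatment holds. Consider a patient whose PSA is rising after radiotherapy but is still below 0.2 ng/ml, and who is put on ADT. No rule has been met. ADT can keep PSA below the threshold, and because imaging is prompted by biochemical or clinical progression, it also removes the usual occasion for finding a new lesion. Under Section 3.3 as written, this patient is progression-free at 2 years.

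Two things are at stake. The 2-year PFS would partly reflect second treatments while being reported as the result of the first. And the primary objective, finding prognostic factors for PFS, would rest on an outcome in which some treatment failures are coded as successes. If start dates of later treatment are not collected, neither problem can be examined afterwards.

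**Working it through.** **Step 1: the plan's own figure.** Section 6.3 assumes a 2-year PFS of 80%, a margin of 6 points and 95% confidence, and states 172 patients, or 180 with 5% dropout. The single-proportion formula gives n = 1.96² × 0.80 × 0.20 / 0.06² = 170.7, so 171, one fewer than stated. Then 171 / 0.95 = 180. The figure reproduces, and this point does not change it.

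**Step 2: can treatment come before an event?** Nothing prevents it. Later ADT is not restricted, and Section 3.3 follows the patient to last follow-up whatever is given. For a nadir above 0.2, two consecutive rises are required. At 3-monthly PSA the second comes about 3 months after the first, which leaves an interval in which treatment can start.

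**Step 3: direction.** Compared with counting new treatment as an event, the written rule can only give the same or a higher 2-year PFS. Compared with what would have happened without the new treatment, PFS is too high to the extent that the treatment delays the PSA rise.

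**Step 4: size, by assumption.** The protocol gives no rate of early new treatment. Let q be the share of patients counted event-free at 2 years who started new treatment first, and s the share of those who should count as failures. Treating 2-year PFS as a simple proportion:

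overstatement in points = 80 × q × s

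With s = 1, every such patient counts as an event. With s = 0.5, only half would otherwise have progressed by 2 years. The number of patients is 0.80 × 172 × q.

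| q (assumed) | Patients of 172 | 2-year PFS, s = 1 | Overstatement, s = 1 | Overstatement, s = 0.5 |
| --- | --- | --- | --- | --- |
| 0% | 0 | 80.0% | 0 | 0 |
| 1% | 1.4 | 79.2% | 0.8 | 0.4 |
| 2% | 2.8 | 78.4% | 1.6 | 0.8 |
| 5% | 6.9 | 76.0% | 4.0 | 2.0 |
| 7.5% | 10.3 | 74.0% | 6.0 | 3.0 |
| 10% | 13.8 | 72.0% | 8.0 | 4.0 |

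With s = 1 the overstatement equals the planned 6-point margin at q = 6 / 80 = 7.5%, about 10 patients. For scale, the plan expects 172 × 0.20 = 34.4 events.

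**Step 5: previously irradiated patients under observation.** The footnote triggers re-staging at one rise of more than 25% over PSA at recurrence. Section 3.3 needs two consecutive rises of more than 25% over nadir when the nadir is above 0.2. The reference value and the number of rises both differ. These patients have also completed no salvage treatment at first relapse, so Section 3.3 does not say when their clock starts. Nor is it stated whether a later bed retreatment belongs to the initial plan.

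**The case against.** The strongest reply is that handling of treatment given before progression is often left to the SAP, which is not at hand, and that following patients regardless of later treatment is a recognised strategy. On that view, making treatment start an event ties the endpoint to unstandardised clinician decisions in a multicentre observational study, and overstatement exists only relative to another estimand. Part of this stands. Following patients regardless would be defensible if chosen deliberately, and dependence on clinician timing is a real cost. But the protocol states no such choice. It fixes both the events and the censoring date, and an SAP cannot use start dates that were never collected. Reporting both definitions answers the estimand objection.

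Four stronger readings are tempting, and the protocol does not support them:

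- *The protocol directs ADT before progression.* It does not. The treatment table assigns ADT by PET/CT findings. Later early ADT is merely not excluded.
- *An observed patient whose bed is later retreated is wrongly kept event-free on a running clock with a new, lower nadir.* The clock start for that patient is undefined, no text resets the nadir, and retreatment is arguably part of the plan.
- *The fastest PSA risers lose the most events.* They may be treated earliest, but at 3-monthly PSA they also cross 0.2 soonest. The net effect cannot be derived.
- *2-year PFS will be overstated by several points.* No rate is given, and zero is possible. Early re-staging that shows a new lesion would count as an event and reduce the effect.

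**Conclusion.** The point holds as a weakness in the definition of the primary endpoint. Followed exactly, Section 3.3 counts a patient as progression-free when new treatment started before a rule was met has kept PSA down, and the items listed in Section 6 would not show that this happened. The direction is clear: 2-year PFS can only be the same as, or higher than, it would be if new treatment counted as an event.

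The size is unknown. Under the assumed range of 0% to 10% of event-free patients, the difference is 0 to 8 points if all are counted as events and 0 to 4 if half would otherwise have progressed. This rests on the plan's 80% and on 2-year PFS treated as a proportion. ADT given as the initial PET-allocated treatment is part of the strategy and is not in question. The change is worth making because it is cheap. The sample size is unaffected.

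**What to change.** - **Section 3.3.** Add as a PFS event, dated at its start, any anticancer treatment (ADT, other systemic therapy, further radiotherapy or surgery) begun for rising PSA or recurrence and not part of the initial PSMA-guided plan. Report the present definition as a sensitivity analysis.
- **Section 6, Evaluation During Treatment.** Record start dates of later ADT, other systemic therapy and local treatment at the existing 3-monthly visits. Continue PSA and imaging records after that date, so that radiological PFS and survival can still be analysed.
- **Section 2 footnotes and Section 3.3.** For previously irradiated patients under observation, reconcile the re-staging trigger with the progression rule, state when PFS starts, and state whether later bed retreatment belongs to the initial plan. Which clinical rule applies is for the investigators to decide.

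The cost is one sentence in the endpoint, a few case report form fields at visits already planned, and the clarification for observed patients. The downside is a possibly slightly lower reported PFS and some dependence on when clinicians choose to treat. The sensitivity analysis would make that dependence visible.
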